### Study settings

This study is conducted in 2 FEP programs in the province of Quebec, Canada. These multidisciplinary clinics admit approximately 200 patients annually, who are followed for up to 3 years on a case management basis. In this clinical model, which is based on a Quebec adaptation of the NICE guidelines for FEP programs [31, 32], each patient is followed by a psychiatrist and a case manager, i.e., the clinician who oversees and coordinates the patient’s care and services. Case managers include trained nurses, occupational therapists, psychologists, social workers and specialized educators. In addition to pharmacological treatments, for which access to pharmacists specialized in mental health is provided, individual psychotherapy, family intervention and community outreach are also offered to patients during their follow-up. An exhaustive systematic clinical follow-up is provided by the case managers, which includes standardized questionnaires and also calls on the input of the patients’ relatives. All these clinical data are rigorously recorded in the patients’ medical files, and then collected and managed by the research staff using the Research Electronic Data Capture (REDCap) platform hosted at Université Laval [33, 34]. No consent to participate in this study is required given the lack of any contact between the patients and the research team (ethics approval obtained at both study sites, #MP-13-2020-1843, NSM).

### Participants

All patients admitted at the 2 study sites during the recruitment period will be included, without any exclusion criteria other than those related to admittance in the clinics (i.e., organic psychosis and severe intellectual disability). Admittance in these clinics requires to be aged between 18 and 35 years old, to have a primary diagnosis of FEP according to DSM-5 criteria (including both affective and nonaffective psychoses) and to have a limited exposure to antipsychotic continuous treatment (i.e., fewer than or equal to 6 months).

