## Methods

### Study design

This is a prospective multicenter cohort study with an expected sample size of 800 patients with a diagnosis of FEP, followed for up to 3 years. The recruitment is ongoing since November 1st, 2019, through November 1st, 2023. All patients admitted at the 2 study sites during this period will be evaluated for PBG by the clinical staff at admission, and every 6 months thereafter, using a screening and assessment procedure developed specifically for this study. The follow-up period will end on May 1st, 2024. During this follow-up, independent variables will be extracted from patients’ medical records by the research staff at admission, and every 6 months afterwards.

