### Dependent variables

The primary outcome is the occurrence of a DSM-5 diagnosis of gambling disorder established by the treating psychiatrist. The secondary outcome is the occurrence of PBG, as defined by a score greater than or equal to 8 on the Problem Gambling Severity Index (PGSI) [3], a reliable and validated screening instrument in general population samples which has also been used in previous studies conducted in patients with psychotic disorders [5, 7, 8]. As previously stated, these outcomes are assessed by the case managers and treating psychiatrists using a screening procedure for PBG that has been developed in collaboration with experts on gambling from the *Centre Québécois d’Excellence pour la Prévention et le Traitement du Jeu*. It is a 3-step procedure that includes (1) a screening questionnaire of gambling habits, (2) an evaluation of the severity of the gambling problematic using the PGSI, and (3) a diagnostic interview assessing the DSM-5 gambling disorder diagnosis. The first 2 steps are carried out by the patients’ case managers, while the last step is conducted by the treating psychiatrist on the basis of all available data, i.e., his or her own clinical interview, information obtained during the screening procedure, and collateral information gathered by the case manager from the patients’ relatives. Results of this procedure are recorded in the patients’ medical files and extracted by the research staff.

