### Independent variables

Variables that will be prospectively extracted from the patients’ medical records include socio-demographic (sex at birth, gender identity, ethnicity, employment status, education level, relationship status, living arrangements, criminal history) and clinical variables (main DSM-5 psychiatric diagnosis, psychotic illness severity as rated by the treating psychiatrist using the Clinical Global Impressions Severity scale, comorbid DSM-5 psychiatric diagnoses, community treatment order, medication treatment, including antipsychotics and all other psychotropic drugs [i.e., antidepressants, benzodiazepines, hypnotics, mood stabilizers, psychostimulants]). Regarding medication, information on both current (i.e., during the follow-up period) and past (i.e., prior to admission in the clinics) drugs will be collected (including dosages, frequency, and route of administration). A patient will be considered exposed to a drug after receiving it for greater than 1 month (or 1 injection in the case of long-acting injectable antipsychotics). Medications administered on an as-needed basis will not be considered. Gambling history (i.e., prior to patients’ admission in the clinics) will be questioned by the case managers as part of the screening procedure for PBG and divided in 3 categories, i.e., none, occasional/recreational, or PBG (i.e., DSM-3 or DSM-4 diagnosis of pathological gambling or DSM-5 diagnosis of gambling disorder). For patients with PBG and/or gambling disorder, the nature of the treatments received for their gambling problematic as well as their effectiveness in resolving it will be documented.

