The major strengths of this study include the large sample size and the length of the follow-up period, which should enable us to generate relevant findings. The population study is also representative of the FEP population of the province of Quebec, in part due to the lack of exclusion criteria and necessity to obtain consent as well as the territories served by the 2 study sites, which contain both urban and rural areas. Furthermore, the fact that no informed consent is required prevents a participation bias. Results of this study should thus be readily generalizable. In addition, the exhaustiveness and rigour of the screening and assessment procedure for PBG, as well as collateral information provided by the patients’ relatives, will ensure that the findings are reliable and less prone to detection bias. The prospective design of the study will also allow for a better examination of potential risk factors for PBG in this population and could add evidence to a possible causal link between aripiprazole use and PBG. To this end, the fact that all patients, notwithstanding the antipsychotic drugs received, will benefit from the same screening procedure for PBG will prevent a surveillance bias. The key limitations to this study are (1) previous findings regarding a possible association between PBG and aripiprazole could lead to a decrease in its use, particularly in patients deemed more at risk by clinicians, and thus introduce a prescribing bias, and (2) evaluation of the study outcomes is dependent on the cooperation of clinicians in following the PBG screening procedure. For the first point, while we have no control over the clinical practices and prescribing patterns of psychiatrists, the study will be extended if 25 cases of PBG have not been observed by the end of the recruitment period, i.e., November 1st, 2023. For the second point, a monitoring committee has been set up to closely and regularly follow up with clinicians to ensure that the screening procedure for PBG is being properly followed. Training in the use of this procedure is also provided to all new clinicians arriving during the study. Taken together, these methodological aspects will lead to results that should significantly deepen our understanding of a neglected comorbidity and hopefully positively impact services and care provided to people with FEP.

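### Patients may enter after up to 6 months of antipsychotic treatment, so the single aripiprazole factor can mix pre-admission with new users and bias the hazard ratio in either direction

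*Protocol article*

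**What the plan says.** All statements are in the protocol article.

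- **Participants.** Admission requires patients "to have a limited exposure to antipsychotic continuous treatment (i.e., fewer than or equal to 6 months". Patients are included "without any exclusion criteria other than those related to admittance in the clinics", so neither existing users of aripiprazole nor existing gambling cases are kept out.
- **Study design.** Patients "will be evaluated for PBG by the clinical staff at admission, and every 6 months thereafter".
- **Dependent variables.** "The primary outcome is the occurrence of a DSM-5 diagnosis of gambling disorder established by the treating psychiatrist". The text does not say that the disorder must be new since admission.
- **Independent variables, drugs.** For medication, "information on both current (i.e., during the follow-up period) and past (i.e., prior to admission in the clinics) drugs will be collected", with dose, frequency and route. "A patient will be considered exposed to a drug after receiving it for greater than 1 month", or after one long-acting injection. Whether time before admission counts toward that month is not said.
- **Independent variables, gambling.** "Gambling history (i.e., prior to patients’ admission in the clinics) will be questioned by the case managers". It has three levels, and the top level requires a formal DSM diagnosis. No onset date is listed.
- **Statistical analyses.** Aripiprazole use is one candidate risk factor, with no distinction between use begun before and after admission. Confounders are to be chosen with a directed acyclic graph.
- **Discussion.** The prospective design "could add evidence to a possible causal link between aripiprazole use and PBG".

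**The concern.** The Background faults the earlier study because its retrospective design prevented assessment of causality. The advantage claimed here is that exposure comes before outcome, under observation. That holds for a patient who starts aripiprazole after admission. It need not hold for one who arrives already treated.

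Take a patient who starts aripiprazole 4 months before admission and begins to gamble problematically 2 months later. The gambling followed the drug, yet both lie before the dividing date. Now take a patient with 4 months of use and no gambling. This patient enters having already passed the early period without an event, whereas a new user goes through that period under observation. A single aripiprazole factor does not separate these patients from new users. At stake is whether the hazard ratio can bear the causal reading that the Discussion hopes for. Neither of the two key limitations listed there, prescribing bias and clinician cooperation, covers this.

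**Working it through.** **1. The plan's own figure.** Statistical analyses gives 25 events for a hazard ratio (HR) of 4, 90% power and two-sided 5%. The share exposed is not stated. Schoenfeld's formula is events = (1.960 + 1.282)² / [p(1 − p)(ln HR)²]. With p = 1/3 (assumed) this is 10.51 / (0.2222 × 1.922) = 24.6, so 25 events, with 90.4% power. With p = 1/2 it gives 22. The figure is reproducible with about one third (or two thirds) exposed and does not depend on the present point.

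**2. What can happen to a case already present at admission after earlier aripiprazole.** The article leaves each of these open:

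| Handling | Effect on the aripiprazole HR |
|---|---|
| Counted as an event, prior use counts as exposure | adds an exposed event: up |
| Counted as an event, prior use does not count | adds an unexposed event: down |
| Removed as a baseline case, or adjusted for as history | a possible drug effect is lost: down |

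**3. Size of an upward shift (illustration).** With 25 events, one third exposed, HR 4 and equal person-time per patient, exposed events are 25 × (4/3) / (4/3 + 2/3) = 16.67 and unexposed events 8.33. The crude ratio is (16.67 / (1/3)) / (8.33 / (2/3)) = 50 / 12.5 = 4. Each further case that falls only in the exposed adds 3 / 12.5 = 0.24. If admission cases fall in both groups, the ratio rises only when they exceed 2 exposed to 1 unexposed (16.67 : 8.33).

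**4. Size of a downward shift from falling risk (illustration).** Assume HR 8 in the first 6 months on drug and 2 afterwards, over 18 months.

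- New users: (6 × 8 + 12 × 2) / 18 = 4.0.
- 3 months of prior use: (3 × 8 + 15 × 2) / 18 = 3.0.
- 6 months of prior use: 2.0.
- Half the exposed prevalent: (4.0 + 3.0) / 2 = 3.5, or (4.0 + 2.0) / 2 = 3.0.

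With HR 6 then 3, the same steps give 3.75 and 3.5. At 25 events and p = 1/3, power is 90.4% at HR 4, 84.0% at 3.5 and 73.5% at 3.0. The events needed for 90% power are 25, 31 and 40.

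The study's own calendar gives the same picture. Uniform entry over 4 years, closure 6 months later and a 3-year cap give a mean follow-up of (1.5 × 3 + 2.5 × 1.75) / 4 = 2.22 years. For HR 8 then 2, the average is (0.5 × 8 + 1.72 × 2) / 2.22 = 3.35 in new users, 2.68 after 3 months of prior use and 2.00 after 6. With half the exposed prevalent, the pooled value is 3.01 or 2.68. With 75% it is 2.84 or 2.34.

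**5. Depletion of susceptible patients (illustration).** Keep an individual HR of 4, take a monthly hazard of 0.064 / 36 in the unexposed and gamma frailty with variance θ. After 6 months of prior use, the HR at entry against unexposed patients whose clock starts at admission is 4 / (1 + θ × 4 × 6 × 0.064 / 36). This is 3.84 for θ = 1 and 3.30 for θ = 5.

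**6. The null case.** With a constant HR of 4 and no heterogeneity, the HR stays 4.0 whatever the share of prevalent users.

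The risk patterns, the prevalent shares and θ are assumptions. The documents give none of them.

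**The case against.** A reader might infer that gambling begun on pre-admission aripiprazole necessarily becomes history, is adjusted away, and leaves surviving users who dilute the HR. The documents do not support that chain. The top history category requires a diagnosis, so an undiagnosed case found at the admission screen could count as an event. A drug begun before admission and continued is current as well as past. Gambling history is not in the listed risk factors, no step adjusts for it or excludes on it, and a directed acyclic graph is meant to keep consequences of exposure out of the adjustment set. The Cox time origin is not stated; admission is a reasonable inference from the screening schedule. Dilution needs risk that falls with time on drug, or depletion. The 6-month limit covers any antipsychotic, so the number of prior aripiprazole users is unknown. All of this stands, and it rules out a claim about direction or size.

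It can also be said that time origin and risk-set rules belong in the full protocol or analysis plan, neither of which is at hand. Their absence from an article is not the finding. What remains is what the article does state: the eligibility rule, the division of both histories at admission, the single aripiprazole factor and the causal aim. Collecting past drugs makes it possible to separate prior users, but the items listed (dose, frequency and route; three undated gambling categories) do not show which came first. Analysis wording alone cannot recover that order.

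Finally, restricting to new users costs events. If half the exposed are removed in the step 1 setting, 8.33 + 8.33 = 16.67 events remain with an exposed share of (1/6) / (5/6) = 0.2. Power at HR 4 is then Φ(√(16.67 × 0.16) × 1.386 − 1.960) = Φ(0.30), about 62%. This is a good reason not to make the new-user estimate the only one.

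**Conclusion.** The point holds as a risk of bias of unknown direction and size. The aripiprazole contrast can mix new users with patients exposed before admission, and some gambling disorder present at admission may follow the exposure. Under assumed front-loaded risk with half the exposed prevalent, an HR of 4 falls to between 3.75 and 3.0. Under constant, homogeneous risk it does not fall. If admission cases count as events and cluster in prior users, it rises. The causal reading in the Discussion is secure in temporal order only for patients who start the drug under observation. The change is worth making because it is cheap and part of it depends on what is abstracted from the records.

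**What to change.** Leave eligibility as it is.

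1. From the past-drug data already collected, classify each patient at admission as never, past or current user of a dopamine partial agonist.
2. Record whether any gambling problem began before or after the first partial-agonist dose. Treat only gambling that preceded that dose as a baseline confounder.
3. Do not count gambling disorder already present at the admission screen as an incident event.
4. Beside the pooled aripiprazole estimate, prespecify a new-user estimate in patients with no partial agonist and no gambling disorder before admission. Report pre-admission users as a separate stratum.
5. Rest the causal interpretation on the new-user estimate.

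The cost is one added abstraction field, some analysis wording and lower precision in the new-user estimate. The pooled estimate is kept.

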### Dependent variables

The primary outcome is the occurrence of a DSM-5 diagnosis of gambling disorder established by the treating psychiatrist. The secondary outcome is the occurrence of PBG, as defined by a score greater than or equal to 8 on the Problem Gambling Severity Index (PGSI) [3], a reliable and validated screening instrument in general population samples which has also been used in previous studies conducted in patients with psychotic disorders [5, 7, 8]. As previously stated, these outcomes are assessed by the case managers and treating psychiatrists using a screening procedure for PBG that has been developed in collaboration with experts on gambling from the *Centre Québécois d’Excellence pour la Prévention et le Traitement du Jeu*. It is a 3-step procedure that includes (1) a screening questionnaire of gambling habits, (2) an evaluation of the severity of the gambling problematic using the PGSI, and (3) a diagnostic interview assessing the DSM-5 gambling disorder diagnosis. The first 2 steps are carried out by the patients’ case managers, while the last step is conducted by the treating psychiatrist on the basis of all available data, i.e., his or her own clinical interview, information obtained during the screening procedure, and collateral information gathered by the case manager from the patients’ relatives. Results of this procedure are recorded in the patients’ medical files and extracted by the research staff.

### Independent variables

Variables that will be prospectively extracted from the patients’ medical records include socio-demographic (sex at birth, gender identity, ethnicity, employment status, education level, relationship status, living arrangements, criminal history) and clinical variables (main DSM-5 psychiatric diagnosis, psychotic illness severity as rated by the treating psychiatrist using the Clinical Global Impressions Severity scale, comorbid DSM-5 psychiatric diagnoses, community treatment order, medication treatment, including antipsychotics and all other psychotropic drugs [i.e., antidepressants, benzodiazepines, hypnotics, mood stabilizers, psychostimulants]). Regarding medication, information on both current (i.e., during the follow-up period) and past (i.e., prior to admission in the clinics) drugs will be collected (including dosages, frequency, and route of administration). A patient will be considered exposed to a drug after receiving it for greater than 1 month (or 1 injection in the case of long-acting injectable antipsychotics). Medications administered on an as-needed basis will not be considered. Gambling history (i.e., prior to patients’ admission in the clinics) will be questioned by the case managers as part of the screening procedure for PBG and divided in 3 categories, i.e., none, occasional/recreational, or PBG (i.e., DSM-3 or DSM-4 diagnosis of pathological gambling or DSM-5 diagnosis of gambling disorder). For patients with PBG and/or gambling disorder, the nature of the treatments received for their gambling problematic as well as their effectiveness in resolving it will be documented.

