### Statistical analyses

Patients’ socio-demographic and clinical characteristics will be detailed using descriptive statistics. Survival analyses using Cox regression models will be performed to identify potential risk factors for both primary and secondary outcomes. Potential risk factors that will be examined include sex at birth, gender identity, ethnicity, employment and relationship status, criminal history, psychiatric comorbidities (i.e., substance-use disorder, personality disorder), the use of aripiprazole, the use of dopamine partial agonists other than aripiprazole (i.e., brexpiprazole, cariprazine) and the use of any dopamine partial agonists. Cox regression models will be constructed for each of these variables to adjust for potential confounding factors identified using the directed acyclic graph approach. In order to detect a hazard ratio greater than 4 between the use of aripiprazole and the primary outcome with a statistical power of 90% and a bilateral significance level of 5%, 25 events are needed through the follow-up period. The hazard ratio of 4 is considered conservative considering that an odds ratio of 8.6 was observed in our previous nested case-control study [8]. The expected sample size of 800 patients is considered sufficient to observe at least 25 cases of gambling disorder (primary outcome) over the follow-up period given the 3-year prevalence of PBG of 6.4% previously revealed in a similar population [8]. As for the nature and the effectiveness of treatments for PBG and/or gambling disorder, this will be documented for all patients who will have developed either the primary or secondary outcome during the study follow-up period using descriptive statistics.

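### The one-month minimum for oral exposure leaves brief users of aripiprazole or another partial agonist, and their events, in the unexposed reference group

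*Protocol article*

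**What the plan says.** The Independent variables section of the protocol article considers a patient "exposed to a drug after receiving it for greater than 1 month (or 1 injection in the case of long-acting injectable antipsychotics". It sets as-needed use aside: "Medications administered on an as-needed basis will not be considered". The point here therefore concerns regular use only. Details of current and past drugs "will be collected (including dosages, frequency, and route of administration".

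The Participants section keeps every patient in the cohort, apart from the clinics' own admission criteria: "All patients admitted at the 2 study sites during the recruitment period will be included, without any exclusion criteria".

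The Statistical analyses section lists among the factors for Cox regression "the use of aripiprazole, the use of dopamine partial agonists other than aripiprazole", and also the use of any partial agonist. The event target is built on the aripiprazole contrast: "In order to detect a hazard ratio greater than 4 between the use of aripiprazole and the primary outcome", with 90% power and a two-sided 5% level, "25 events are needed through the follow-up period".

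Under Study design, patients are "evaluated for PBG by the clinical staff at admission, and every 6 months thereafter".

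No section names the reference group, gives brief oral users a category of their own, says whether exposure varies over time, or says how long exposure is taken to last after a drug is stopped.

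**The concern.** The stated rule has one threshold and two outcomes: exposed, or not. Someone who takes oral aripiprazole every day for up to a month and then stops never crosses it. Since that person is not excluded and no third group is described, a use versus non-use contrast puts them with patients who never took the drug. This is so whether exposure is coded once per patient or as a time-varying covariate, because in neither case does the patient reach exposed status.

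The reference group should represent the hazard without the drug. If a short course carries some of the risk under study, the reference hazard is raised and the hazard ratio shrinks toward 1. Gambling is assessed every 6 months, so a problem that began during a short course may be recorded months after the drug was stopped, as an event in a patient coded as unexposed.

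The aripiprazole contrast is part of the main hypothesis and sets the event target. With 25 events planned, the placement of one, two or three cases can move the estimate noticeably.

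**Working it through.** **Inputs from the article.** Hazard ratio 4, power 90%, two-sided level 5%, 25 events (all Statistical analyses); the one-month rule (Independent variables).

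**Inputs that are assumed.** The article gives neither the exposed share nor the share of brief users.

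**Step 1: the plan's own figure.** Schoenfeld's formula is events = (1.960 + 1.282)² / [p(1 − p)(ln 4)²], where p is the exposed share. The numerator is about 10.51 and (ln 4)² is about 1.922.
- p = 1/3: 10.51 / (0.2222 × 1.922) = 24.6, rounded up to 25.
- p = 1/2: 10.51 / (0.25 × 1.922) = 21.9, rounded up to 22.

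The stated 25 is reproduced with about one third exposed (or, by symmetry, two thirds). One third is used below. It is an assumption that fits the plan's figure, not a figure from the article.

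**Step 2: expected split of events.** With exposed to unexposed person-time of 1 to 2 and a hazard ratio of 4, exposed events are 25 × 4 / (4 + 2) = 16.67 and unexposed events are 8.33. Check: (16.67/1) / (8.33/2) = 4.0.

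**Step 3: move a share of the exposed cases to the reference.** Two versions bracket what person-time might do.

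| Share moved | Events moved | Person-time moves in proportion | Only events move |
|---|---|---|---|
| 5% | 0.83 | (15.83/0.95) / (9.17/2.05) = 3.73 | (15.83/1) / (9.17/2) = 3.45 |
| 10% | 1.67 | (15/0.90) / (10/2.10) = 3.50 | (15/1) / (10/2) = 3.00 |
| 20% | 3.33 | (13.33/0.80) / (11.67/2.20) = 3.14 | (13.33/1) / (11.67/2) = 2.29 |

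The middle column describes brief users who carry the same hazard as sustained users and stop for reasons unrelated to gambling. The right-hand column is the extreme, close to what would happen if only patients who become cases stopped early.

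**Step 4: dependence on the risk from brief use.** Let m be the share of reference person-time that comes from brief users and h their hazard ratio against never users. The observed hazard ratio is 4 / (1 − m + m·h).
- h = 1: 4.0 whatever m is, so no bias.
- h = 2: m = 2%, 5%, 10%, 20% gives 3.92, 3.81, 3.64, 3.33.
- h = 4: the same values of m give 3.77, 3.48, 3.08, 2.50.

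This agrees with Step 3: moving 5% of exposed person-time makes m = 0.05/2.05 = 2.4%, and with h = 4 the result is 4 / (1 + 3 × 0.0244) = 3.73.

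**Step 5: power at 25 events.** Taking the exposed share at which 25 events give 90% power (0.323), the power under Step 4 is 89%, 88%, 86%, 80% for h = 2 and 87%, 83%, 75%, 57% for h = 4. Moving 1, 2 or 3 whole cases, events only, gives hazard ratios of 3.36, 2.85, 2.42 and power of 81%, 69%, 54%.

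**The case against.** **The route difference.** A reader might infer that the fault lies in counting one injection at once while oral use must exceed a month. The article does not support that. The one-injection rule is limited to long-acting products, and one such injection can coherently stand for sustained use. A one-month minimum for every route would place brief oral users in exactly the same group. This objection stands in full.

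**Stopping because of gambling.** A reader might also infer that the misclassification is known to depend on the outcome. The article neither describes nor quantifies withdrawal within a month because of gambling. With scheduled assessment every 6 months, such a withdrawal would usually need detection between visits. The Discussion raises reduced prescribing in patients thought to be at risk, which is a different matter. It suggests that prescribers may act on gambling risk, so early stopping for this reason is plausible, but no more than that.

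**Certainty and size of the bias.** The bias vanishes if brief use carries no excess risk, and every share used above is assumed. The 2.3 is a worst case; it becomes about 3.1 when person-time moves with the events. This stands.

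**What an article leaves out.** The reference group is not named, and a full protocol or analysis plan that is not shown may treat brief users separately. This stands in part. Placement in the reference is the consequence of applying the printed rule to all patients in a use versus non-use contrast, not something the article says outright. The rule itself is printed, however, and provides for no third group.

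**The purpose of a minimum duration.** It keeps short trials of a drug from diluting the exposed group, and starting exposure at the first dose would exchange one misclassification for another. That is a good reason to keep the rule for defining the exposed. It is no reason to use brief users as the unexposed comparison.

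**Conclusion.** The point holds as a weakness in a stated definition, not as a contradiction or a wrong figure. Applied literally, the oral threshold leaves patients with one month or less of regular use of aripiprazole or another partial agonist, and their events, in the unexposed reference. Any resulting bias is toward 1. It is conditional on brief use carrying excess risk or on early stopping because of gambling, and it is nil if brief use carries no excess risk.

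Its true size cannot be computed, because the share of brief users is not given. With a true hazard ratio of 4, one third exposed and 25 events, the illustrative range is 3.7 down to 3.1 for 5% to 20% of exposed cases when person-time moves in proportion, and 3.5 down to 2.3 when only events move. The second range should be read as an outer limit. The small event target is what makes a few misplaced cases matter, and the remedy is cheap enough to be worth adopting on that ground.

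**What to change.** Keep the one-month definition for the primary exposure, including the one-injection rule for long-acting products. Add a statement that regular oral use of one month or less is coded as a separate category outside the unexposed reference, for aripiprazole, for the other partial agonists and for the combined class. Add one sensitivity analysis in which exposure starts at the first regular dose or injection. As-needed use stays excluded.

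The medication records already being extracted should serve. The article lists dosage, frequency and route but not start and stop dates; a one-month rule implies that duration is recorded, and this should be confirmed.

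The cost is one sentence in the definition, one extra category and one extra model. The reference group becomes slightly smaller, and with about 25 events the extra category will be sparse and imprecisely estimated, so its own hazard ratio should not be over-read. The change concerns the analysis only and does not touch patient care.
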